### Statistical analysis

The main analysis will be based on intention to treat in that participants will be analysed according to the group to which they were allocated irrespective of the extent of intervention received. The primary outcome, risk of repeat falling over the 6 month period after randomisation, will be compared between intervention and control groups using a logistic regression model including falling during the pre-randomisation monitoring period, Hoehn and Yahr score, and centre as covariates, with the definition of the falling covariate decided at blind review of the data prior to analysis.

Repeat falling during 6–12 months and other binary secondary outcomes will be examined using logistic regression models similar to that for the primary outcome. The rates of falling over 0–6 months and over 6–12 months will be examined in negative binomial models including baseline rate of falling over the 3 month pre-randomisation falls collection period, Hoehn and Yahr score, and centre as covariates, fitted using either the *nbreg* or *xtpoisson* regression commands in Stata (Statacorp, TX, USA). In the negative binomial model, the effect of the intervention is summarised as a falls incidence rate ratio (IRR) (intervention/control) with ratios below 1.00 indicative of lower rates in the intervention group. All participants in the main trial will have been asked to complete the baseline three months falls collection, and the length of follow-up time over which falls events are collected between 0–6 months and 6–12 months post randomisation will be included as exposure times in the regression. Rates of falling in each of the three month periods between the pre-randomisation period and 12 months in the intervention and control groups will be displayed graphically. Other secondary outcomes will be examined in mixed normal models for repeated measurements at 3, 6 and 12 months controlling for centre, Hoehn and Yahr score, and baseline value, including participants with incomplete follow-up information in the analysis. No formal interim analyses are planned.

Sensitivity analyses will be conducted to examine the impact of missing data due to causes other than death, using worst-case and other single imputation on conclusions. Since only participants successfully completing the initial three months falls diary collection period will be entered into the main trial, this should minimise loss of diary information on which the primary outcome is based.

Pre-planned subgroup analyses of the primary outcome will be performed with subgroups of participants defined by disease severity, phenotype and cognitive impairment, with subgroups specified without reference to the treatment allocation variable and before the blind is broken. The significance of any difference in treatment effect between subgroups, will be examined in a test for interaction. We will also examine the effect of the intervention separately in each centre. The extent of intervention that was received by participants will be described. A secondary per-protocol analysis of the main treatment effect will be conducted, restricting the participants included in the intervention group to those receiving an adequate extent of the intervention, to be decided a priori. If we fail to show a statistically significant difference in the primary ITT analysis, the per-protocol analysis will help in understanding whether the lack of significance resulted from dilution of the treatment effect. Exploratory analysis of the outcome in relation to the main components of the intervention will also be undertaken.

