### Sample size

The primary outcome is the risk of repeat falling between 0–6 months. In a previous trial of PwP with two or more falls in the previous year [16], the risk of repeat falling at six months was 68 % (42/63) for controls versus 56 % (35/63) in the exercise group. However, the population in the proposed trial will include those with one or more previous falls and we therefore anticipate the risk of repeat falling to be lower. Assuming a control group risk of repeat falling between 0–6 months to be 63 %, and 50 % in the intervention group, a sample size of 228 participants per group (n = 456 total) with data for analysis is indicated. Allowing for 10% drop out between agreeing to the 3 months pre-randomisation fall data collection and randomisation, and 5 % of loss to follow-up at 6 months amongst those randomised, a total of 534 participants need to be recruited. We aim to recruit 600 participants. Figure 1 provides a flow diagram showing anticipated numbers at recruitment and follow-up.

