### Physiotherapist training

Physiotherapists will deliver the intervention in participants’ homes across the four study centres. In order to minimise inter-therapist variation and enhance fidelity, a detailed training programme has been developed that includes clinical reasoning for prescribing the exercises and strategies and practical delivery of the programme. This is delivered in a two-day face-to-face session. Once trained and delivering the intervention there will be regular team meetings including masterclass sessions, case studies, and weekly telephone support from the lead physiotherapist.

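### The primary and falls-rate models and the sample size treat participants as independent although physiotherapists deliver the intervention, so the treatment-effect standard error can be too narrow

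*Protocol article*

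**What the plan says.** **Analysis.** Under Statistical analysis, the primary outcome "will be compared between intervention and control groups using a logistic regression model including falling during the pre-randomisation monitoring period", plus Hoehn and Yahr score and centre. The rates of falling use negative binomial models with the baseline rate, Hoehn and Yahr score and centre, fitted with one of two named Stata commands. No therapist term or therapist-level variance is part of these models.

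**Sample size.** The assumed risks of repeat falling are 63% in controls and "50 % in the intervention group", giving "a sample size of 228 participants per group" with data. After allowances of 10% before randomisation and 5% for "loss to follow-up at 6 months amongst those randomised", "a total of 534 participants need to be recruited". The aim is 600.

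**Delivery.** Under Interventions, a physiotherapist assesses each intervention participant, tailors the programme and delivers up to twelve one-hour sessions over six months, with the exact pattern negotiated between the two. Controls have one physiotherapist visit and a DVD before the twelve-month assessment. Under Physiotherapist training, the article recognises that therapists may differ: "In order to minimise inter-therapist variation and enhance fidelity, a detailed training programme has been developed".

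**The concern.** Participants treated by the same physiotherapist share that therapist's skill, choices and persistence. Their outcomes may therefore be correlated, and in this design that correlation arises essentially in one arm. A model that assumes independence counts each intervention participant as a full separate piece of information. If there is positive correlation, the standard error is too small, the confidence interval too short and the p-value too low, for the primary outcome and the falls rates alike. A significant result could then owe something to a few effective therapists, which matters because the Discussion looks ahead to improving physiotherapy care generally.

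The centre covariate does not repair this. A centre main effect removes differences between centres that both arms share. It does not remove variation between therapists that exists only in the intervention arm.

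**Working it through.** **1. Reproduce the stated sample size.** Inputs from the Sample size section: risks 0.63 and 0.50, difference 0.13. The article does not state alpha, sidedness or power; two-sided 5% and 80% power are inferred because they return the stated figure. With mean risk 0.565:

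n = [1.96·√(2·0.565·0.435) + 0.8416·√(0.63·0.37 + 0.50·0.50)]² / 0.13² = (1.3741 + 0.5850)² / 0.0169 = 227.1, rounded up to **228**.

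Recruitment: 456 / 0.95 / 0.90 = 533.3, rounded up to **534**. Both figures follow from independence plus the two dropout allowances, so neither contains room for clustering.

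**2. Numbers at the recruitment target.** 600 × 0.90 × 0.95 = 513, about 256 per arm. Power under independence is then 84.5%.

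**3. Allow for therapists in the intervention arm only.** Assume k therapists with equal caseloads and one therapist per participant. With n per arm:

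- caseload m = n/k; design effect DE = 1 + (m − 1)·ICC
- true/model SE at the null = √[(1 + DE)/2]
- type I error of the stated analysis = 2·[1 − Φ(1.96 / SE ratio)]
- power of a corrected analysis = Φ[(0.13 − 1.96·SE₀)/SE₁], where SE₀ = √[0.565·0.435·(1 + DE)/n] and SE₁ = √[(0.2331 + DE·0.25)/n]

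**4. Middle case: 12 therapists, ICC 0.02, 256 per arm.** m = 21.33 and DE = 1 + 20.33 × 0.02 = 1.407. SE ratio = √(2.407/2) = 1.097. Type I error = 2·[1 − Φ(1.787)] = **7.4%**. SE₀ = 0.0481 and SE₁ = 0.0478, so corrected power = Φ[(0.13 − 0.0942)/0.0478] = Φ(0.75) = **77%**. The stated model, with its smaller null SE of 0.0438, has power Φ[(0.13 − 0.0859)/0.0478] = Φ(0.92) = 82%. The 7.4% and the 77% therefore belong to different analyses.

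**5. Range over the assumptions.**

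| Therapists | ICC | SE ratio, 228/arm | Type I, 228/arm | SE ratio, 256/arm | Type I, 256/arm | Corrected power, 256/arm |
|---|---|---|---|---|---|---|
| 24 | 0.005 | 1.01 | 5.2% | 1.01 | 5.3% | 84% |
| 24 | 0.01 | 1.02 | 5.5% | 1.02 | 5.6% | 83% |
| 12 | 0.005 | 1.02 | 5.5% | 1.03 | 5.6% | 83% |
| 12 | 0.02 | 1.09 | 7.1% | 1.10 | 7.4% | 77% |
| 16 | 0.05 | 1.15 | 8.9% | 1.17 | 9.5% | 72% |
| 8 | 0.05 | 1.30 | 13.1% | 1.33 | 14.1% | 61% |

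With k fixed, more recruitment means larger caseloads, so it restores some power but raises the type I error slightly.

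**6. Check on the centre covariate.** I simulated a logistic model with centre as a fixed effect: four centres, 12 therapists nested in them, no average effect, 256 per arm, 10,000 runs. Type I error was 7.6% at ICC 0.02 against 5.3% at ICC 0. The centre term gave no protection.

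**The case against.** The best case against has four parts.

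- **It may be left to the analysis plan.** Sensitivity analyses and variance estimators commonly are, and the plan is not shown. This stands for anything the article merely omits. But the article writes out the models with their covariates and even names the software commands. What it openly leaves for later is the definition of the falling covariate, the subgroups and the per-protocol threshold, not the error structure.
- **No figure in the article fixes the size.** This stands. There is no therapist number, caseload or ICC. Two-day training, masterclasses, weekly support and fidelity visits may make the residual ICC small, and at the mild end of the table the effect is negligible.
- **Power has a margin.** This stands in part. Aiming for 600 rather than 534 gives about 256 per arm, and corrected power in the middle case is 77%, against 73% at 228. The margin does nothing for the standard error.
- **The stated model is adequate for these particular therapists.** True if the conclusion is confined to them. The Discussion reaches further.

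A reader might infer more than the article supports: that outcomes do cluster and the standard error is understated as a matter of fact; that type I error is near 13%, which needs the worst value of both assumptions together; that only a few physiotherapists are used; or that the treating therapist is not recorded. The article says none of these things.

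**Conclusion.** The point holds in conditional form. The stated models and sample size assume independence, while delivery by therapist in one arm makes positive correlation plausible. If it is present, intervals and p-values for the primary and falls-rate outcomes are too optimistic. The result depends on assumed therapist numbers and ICCs, equal caseloads, one therapist per participant, and a null under which the average effect is zero but therapists differ. If therapists do not differ at all, the stated test is valid. In the middle case the distortion is moderate: 7.4% type I error for the stated model, or a fall in power from 84.5% to 77% when the analysis is corrected. This does not show that the primary result would mislead. It shows that the reader could not tell without a therapist-level analysis.

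**What to change.** Record the treating therapist for each intervention participant, if this is not already done, with a rule for participants seen by more than one. Before the blind is broken, pre-specify a partially nested model for the primary and falls-rate outcomes: a therapist random effect in the intervention arm only, controls treated as independent, and a small-sample correction because the number of therapists may be small. It should be at least a named sensitivity analysis. Report the therapist ICC with its interval, the number of therapists and their caseloads.

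The cost is one identifier per intervention participant, one extra model per outcome and slightly wider intervals. Recruitment need not change.

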### Recruitment

Potential participants will be identified from clinical registers of PD specialists at each site, research registers of those who have previously indicated interest in taking part in future research, and from Parkinson’s UK local groups, supported by the National Institute for Health Research (NIHR) Clinical Research Network (CRN). Those identified from clinical registers will be invited to participate, in writing, by their specialist, and those expressing an interest will be asked for permission to pass their contact details onto the research team in order that further information can be shared, and the opportunity to participate offered. All potential participants will be provided with a Participant Information Sheet, a reply slip and pre-paid envelope. On receipt, those expressing interest will be contacted by telephone by the research team to confirm eligibility and offered a home visit (allowing at least 24 hours for consideration before proceeding) to gain written informed consent and complete screening measures. Once consent is gained, demographic data, medical history, MMSE, Montreal Cognitive Assessment (MoCA) [27], Hoehn & Yahr score and number of falls in previous year will be collected and participants will be given diaries to complete for three months to prospectively record any fall events. Permission at this time will also be sought to pass details of those randomised to the intervention arm to a qualitative researcher in order that contact can be made to discuss involvement within the nested qualitative study (see below). Where appropriate, carers will also be invited to participate in the study and will be provided with a carer information sheet. Recruitment commenced in July 2014.

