### Nested qualitative study

A longitudinal qualitative study will be conducted alongside the main trial to explore the impact of Parkinson’s on daily life and the expectations and experiences of participants allocated to the intervention study arm. The study will draw on the principles of grounded theory [48,49] and use a maximum variation sampling strategy [50] addressing age (≤ 80 years; > 80 years), gender, falls in previous year (1 fall; 2–10 falls; > 10 falls), disease severity (each of Hoehn and Yahr stages 1–4) and centre (Southampton, Portsmouth, Bournemouth, Exeter). Semi-structured interviews [51] using a topic guide will be conducted with forty participants (ten from each study site) or as many as needed to ensure data saturation, from the intervention arm of the study, in their own home. Each participant will be interviewed twice, firstly after screening but before the intervention commences, and secondly, six months after completion of the intervention. All interviews will be digitally recorded, transcribed verbatim and supplemented by a researcher diary [52]. Analysis will comprise initial, focused, axial and theoretical coding in order to develop interpretive theories conceptualising the experience of participating in PDSAFE. The qualitative researcher will keep a research diary throughout, and will compare coding of initial interviews with a second researcher to promote sensitivity and reflexivity [52]. Supervisory meetings will ensure that preliminary interpretation is open to scrutiny, and that each iteration is shared and tracked. These strategies will help to ensure that rigour is maintained in the conduct and analysis of this sub-study. Along with self-reported dairies of home exercises, the longitudinal qualitative study will contribute more detailed information about factors influencing adherence.

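### Previous-year falls are recorded for every participant but left out of the falls models; adding them as a pre-specified covariate is a free, though modest and uncertain, gain in efficiency

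*Protocol article*

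**What the plan says.** At screening, the Recruitment section states that the "number of falls in previous year will be collected" from each consenting participant. At least one such fall is also an inclusion criterion (Participants). Beyond eligibility, the only use the article gives it is the sampling frame for interviews, banded as "falls in previous year (1 fall; 2–10 falls; > 10 falls" (Nested qualitative study).

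The Statistical analysis section names its covariates. The primary analysis is a "logistic regression model including falling during the pre-randomisation monitoring period, Hoehn and Yahr score, and centre as covariates". Repeat falling at 6–12 months uses a similar model. Fall rates are analysed in "negative binomial models including baseline rate of falling over the 3 month pre-randomisation falls collection period, Hoehn and Yahr score, and centre as covariates". One item is left to blind review: how the falling covariate in the logistic model is defined. That covariate is tied to the pre-randomisation monitoring period, so the clause does not extend to previous-year falls. The section on pre-randomisation fall data confirms that the diary is meant to serve as a covariate.

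**The concern.** Three months is a short window for classifying people whose outcome is repeat falling over six months. In one set of simulations (assumed inputs, at the planned size and risks), 54–59% of participants recorded 0 or 1 fall in the run-in, although more than half went on to fall repeatedly. A 12-month count covers four times as long and can separate people whom the run-in groups together.

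Randomisation is stratified by site alone, so chance imbalance in fall history is corrected only through the covariates. The Background describes earlier falls trials in this population as mostly non-significant, so power already paid for by data collection is worth using. What is at stake is only the increment over the run-in count, since every falls model already contains that count.

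**Working it through.** **1. The plan's own figure.** The inputs are in Sample size: "Assuming a control group risk of repeat falling between 0–6 months to be 63 %, and 50 % in the intervention group". The article states neither alpha nor power, so I assume 5% two-sided and 80%.

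n per group = [z₁√(2p̄q̄) + z₂√(p₁q₁ + p₂q₂)]² / (p₁ − p₂)², with p̄ = 0.565
= [1.960 × √0.49155 + 0.8416 × √0.4831]² / 0.13²
= (1.374 + 0.585)² / 0.0169 = 227.1, so 228.

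This agrees with "a sample size of 228 participants per group (n = 456 total) with data for analysis is indicated". Recruitment: 456 / (0.95 × 0.90) = 533.3, so 534, also as stated. Unadjusted power at 228 per group is 80.2%. The target of 600 leaves 600 × 0.90 × 0.95 = 513 evaluable, with 84.6% power. No covariate enters any of these figures.

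**2. Increment over the run-in count, with rates that drift.** The documents give no associations, so every input below is an assumption. Each person has seven quarters: four of history, one of run-in and two of follow-up. The log fall rate is a stable person effect (SD *b*) plus a component that drifts from quarter to quarter (SD *a*, adjacent-quarter correlation *ρ*). Entry requires at least one prior-year fall. Risks are calibrated to 63% and 50%, with 456 participants. Recall error is on the log scale, and the recalled count is at least 1. Both models contain treatment and log(1 + run-in falls); the second adds log(prior-year falls). Hoehn and Yahr score and centre are omitted. There were 500 trials per scenario (120 for the negative binomial fits). Arrows run from without to with the prior-year count.

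| b / a / ρ / recall SD | Power | SE of log OR | SD of standardised risk difference | Variance of log IRR |
|---|---|---|---|---|
| 1.2 / 0.5 / 0.5 / 0 | 0.868 → 0.922 | 0.221 → 0.239 | 0.0404 → 0.0377 | −24.1% |
| 1.2 / 0.5 / 0.5 / 0.7 | 0.868 → 0.898 | 0.221 → 0.231 | 0.0404 → 0.0393 | −12.6% |
| 0.8 / 0.9 / 0.7 / 0 | 0.862 → 0.876 | 0.211 → 0.218 | 0.0430 → 0.0416 | −7.6% |
| 0.8 / 0.9 / 0.7 / 0.7 | 0.862 → 0.870 | 0.211 → 0.215 | 0.0430 → 0.0420 | −4.7% |
| 0.5 / 1.1 / 0.7 / 0.7 | 0.856 → 0.854 | 0.206 → 0.208 | 0.0437 → 0.0433 | −1.7% |
| 0.5 / 1.1 / 0.7 / 1.2 | 0.856 → 0.860 | 0.206 → 0.207 | 0.0437 → 0.0435 | −1.0% |

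The Monte Carlo error of a power near 0.86 is √(0.86 × 0.14 / 500) = 0.016, so the fall of 0.002 in one row is noise.

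**3. The same increment as effective participants.** Gain = (z with / z without)² − 1, from mean z.

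- Between-person SD 1.0–1.5, drift 0.3–0.5, recall SD 0.5–1.2, run twice independently: 5–14% in one set and 3–10% in the other. At the top, mean z goes from 3.22 to 3.44, a squared ratio of 1.14.
- Drift accumulating from prior year to run-in to follow-up: SD 1.0, drift 0.5, recall 1.2 gives 2.6%; SD 1.5, drift 0.8, recall 1.0 gives 2.1%; SD 1.0, drift 0.8, recall 1.0 gives 1.0%; SD 1.0, drift 1.0, recall 1.2 gives 0.5%. Favourable values (drift 0.3, recall 0.5) give 8–10%.

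In participants, this runs from 0.005 × 456 = 2 to 0.143 × 456 = 65.

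**4. Rate models.** With low drift the variance ratio was 1.19–1.35, a reduction of 1 − 1/1.19 = 16% to 1 − 1/1.35 = 26%. With accumulating drift it was 1.02–1.27, a reduction of 2% to 21%. A gamma-distributed rate model gave 9–16% with recall SD 0.7. Reductions of 33% and 43% appeared only with perfectly stable rates and perfect recall, which I set aside as implausible.

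**5. Room for one more parameter.** Expected non-repeat fallers: 0.435 × 456 = 198. Overfitting is not a concern.

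**The case against.** The strongest reply is that nothing here is wrong. Every falls model already adjusts for fall history, and the chosen measure is recent and prospectively recorded. The alternative is a 12-month recalled count, cut off below 1 by eligibility and ending about three months before randomisation. Preferring the diary is legitimate, the extra gain cannot be derived from the documents, and the design needs no covariate gain to reach its target. A fuller analysis plan, not shown, may also use the count.

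Most of this stands. The omission is neither a contradiction nor a source of bias. What does not follow is that the count adds nothing once the run-in is in. The mean test statistic rose in every scenario where it was examined, though sometimes trivially. Nor is this simply silence in a condensed article, since the covariates are listed by name.

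A reader might go further and infer three things that the material does not support:

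- *Both models lose precision.* This is true of the rate models only. In the logistic model a prognostic covariate raises the standard error of the conditional log odds ratio (0.221 to 0.239 in the first row of the table) while moving the estimate further from the null. The benefit is power, or a tighter standardised risk difference.
- *A worthwhile gain is assured even with very poor recall.* A floor of 5% for the primary test, or 16% for the rate models, does not survive drift combined with recall error.
- *The trial is underpowered without the count.* The 228 per group stands as an unadjusted calculation.

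**Conclusion.** The point holds as an optional efficiency improvement, not as a defect. For the primary test the gain beyond the run-in count is about 0–14% more effective participants, or 0 to about 5 power points; the top of the power range needs perfect recall. For the rate models it is a reduction of about 1–25% in the variance of the log rate ratio. Both ranges rest wholly on assumed between-person variation, drift and recall error, and both approach zero when rates drift and recall is poor. Because the cost is negligible and no material loss appeared in any scenario, the change is worth making even though its benefit may prove small.

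**What to change.** In Statistical analysis, add log(number of falls in the previous year), as recorded at screening, as a fixed covariate alongside the run-in falls covariate, Hoehn and Yahr score and centre. Apply it to the primary logistic model, the 6–12 month repeat-falling model and both negative binomial models. Eligibility guarantees a count of at least 1, so the logarithm is defined.

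State this before any outcome data are reviewed. The conditional odds ratio changes with the covariate set, so the choice must not be open once results are visible. If the gain is to show as precision in the primary result, report a standardised risk difference beside the odds ratio.

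The cost is one sentence and one parameter per model, with no new data and no change to the sample size.

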An individualised booklet of exercises will be provided, selected from a menu following assessment. If an individual struggles in achieving a good technique the physiotherapist will video record them doing the exercises correctly using a tablet device. This recording will be shared with the participant to provide them with an accurate visual reference when practising. Participants will be encouraged to perform all exercise components daily. However, to avoid the possibility of overload, a daily safety questionnaire is completed, that advises participants which components to complete and which to leave, due to the risk of fatigue or other safety issues.

The intervention will take place over a six-month period and will consist of up to twelve, one hour face-to-face sessions with the physiotherapist. These face-to-face sessions will be delivered more intensely to start but less frequently over time to maximise motivation and promote independence. The exact delivery of these, however, will be negotiated between the physiotherapist and participant. This model of delivery is unique in exercise studies for PwP. An example delivery model could be:Twice a week for weeks 1–2Once a week on week 3, 4, and 5Once a month at 2, 3, 4, 5 and 6 months.

Participants in the control group will continue to receive usual care and will be advised to continue any activities in which they usually participate, but not to commence new activities, if possible. In addition, they will be visited once by a physiotherapist within four weeks of completing pre-randomisation fall diaries and provided with a DVD about Parkinson’s. After the twelve month follow-up assessment has been completed, they will receive written and verbal guidance on physical activity and strategies by the physiotherapist.

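### The per-protocol contrast restricts only the intervention arm by dose received, so it cannot separate dilution from selection when the ITT result is not significant

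*Protocol article*

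**What the plan says.** The Statistical analysis section makes ITT the main analysis: "participants will be analysed according to the group to which they were allocated irrespective of the extent of intervention received". The primary logistic model adjusts for "falling during the pre-randomisation monitoring period, Hoehn and Yahr score, and centre as covariates".

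The same section then adds a per-protocol comparison, labelled secondary, and defines it by "restricting the participants included in the intervention group to those receiving an adequate extent of the intervention, to be decided a priori". It mentions no restriction on the control arm and does not say whether the primary model's covariates carry over. It gives the analysis a purpose: if the ITT result is not significant, "the per-protocol analysis will help in understanding whether the lack of significance resulted from dilution of the treatment effect".

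The Interventions section bears on how dose arises. A daily questionnaire "advises participants which components to complete and which to leave, due to the risk of fatigue or other safety issues", and the timing of the face-to-face sessions is negotiated with each participant over six months. Controls have no counterpart to this dose: "they will be visited once by a physiotherapist within four weeks of completing pre-randomisation fall diaries", and they receive a DVD.

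**The concern.** Randomisation makes the two whole arms comparable. It does not make a dose-selected part of one arm comparable with the whole of the other. Removing under-dosed participants from the intervention arm leaves in the control arm the people who would have been under-dosed had they been allocated to the programme.

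Dose received may be related to fall risk in two ways. Fatigue and safety problems can reduce the exercise done. The dose window is also the outcome window: the programme lasts six months, and the primary outcome is repeat falling over months 0–6. Someone who falls early, is injured and misses sessions contributes both a low dose and outcome events. That person could be dropped from the intervention arm, while the matching control stays in.

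What is at stake is the interpretation of a null trial. The analysis is called on exactly when the ITT result is not significant. A per-protocol difference larger than the ITT difference could then be put down to dilution when selection explains it equally well.

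**Working it through.** **Inputs from the document (Sample size section).** "Assuming a control group risk of repeat falling between 0–6 months to be 63"%, 50% in the intervention group, 228 per group with data.

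**Reproducing the plan's figure.** The article does not state alpha and power. With two-sided 5% and 80% power assumed, pooled variance and no continuity correction:

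n = [1.96 × √(2 × 0.565 × 0.435) + 0.842 × √(0.63 × 0.37 + 0.50 × 0.50)]² / 0.13² = 227.1, rounded up to 228. This matches, so the same figures are used below.

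**Inputs not in the document (assumed).** q is the share of the intervention arm with adequate dose, from 0.6 to 0.9. The gap is the risk of non-adherers minus that of adherers in the absence of any effect, mainly 10 to 20 points, with one negative value.

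**Case 1: no true effect.** The intervention arm's overall risk is 63%, so:

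- adherer risk = 0.63 − (1−q) × gap
- per-protocol difference = −(1−q) × gap
- chance of a significant result in favour of PDSAFE = Φ[((1−q) × gap − 1.96 × SE₀) / SE₁]. SE₀ is the pooled and SE₁ the unpooled standard error, with 228 controls and 228q adherers, unadjusted. The nominal value is 2.5%.

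Worked example, q = 0.7 and gap = 0.20: adherer risk = 0.63 − 0.3 × 0.20 = 0.57; 228 × 0.7 = 159.6 adherers; SE₀ = 0.0504; SE₁ = 0.0506; (0.06 − 1.96 × 0.0504)/0.0506 ≈ −0.77; probability 0.22.

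| q | gap (points) | adherer risk | difference (points) | odds ratio | false benefit |
|---|---|---|---|---|---|
| 0.9 | 10 | 62.0% | −1.0 | 0.96 | 4.0% |
| 0.9 | 20 | 61.0% | −2.0 | 0.92 | 6.3% |
| 0.8 | 10 | 61.0% | −2.0 | 0.92 | 6.1% |
| 0.8 | 20 | 59.0% | −4.0 | 0.85 | 12.9% |
| 0.7 | 10 | 60.0% | −3.0 | 0.88 | 8.7% |
| 0.7 | 20 | 57.0% | −6.0 | 0.78 | 22.1% |
| 0.6 | 20 | 55.0% | −8.0 | 0.72 | 32.7% |
| 0.7 | −10 | 66.0% | +3.0 | 1.14 | 0.5% |

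In the last row adherers are the riskier group and the bias runs against PDSAFE.

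**Case 2: a true effect of −13 points in adherers and none in others, q = 0.7.**

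- ITT difference = 0.7 × (−13) = −9.1 points, whatever the gap.
- Planned contrast = −13 − 0.3 × gap: −19, −16, −13, −10 and −7 points for gaps of +20, +10, 0, −10 and −20.
- CACE = ITT/q = −9.1/0.7 = −13 points in every case, provided allocation has no effect on non-adherers.

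The planned contrast recovers the effect in adherers only when the gap is zero, and nothing in the contrast itself shows whether it is.

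**The case against.** The other side has real points.

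- **The wording is modest.** The plan says the analysis will help in understanding dilution, not that it will establish it. The analysis is secondary and ITT stays primary. The extent of intervention received will also be described, and the qualitative study adds information on adherence. A reader might infer that the plan would conclude that the programme works when taken; no passage says so.
- **The direction is not given.** A reader might also infer that the contrast must favour PDSAFE even with no effect. The document reports no relation between dose and fall risk, and negotiated sessions could go more to higher-risk people. The direction is therefore conditional on who is under-dosed.
- **The questionnaire may not decide who is excluded.** It governs daily exercise components. If adequate extent is defined by physiotherapist sessions, the link is indirect. The overlap of the dose and outcome windows remains under either definition.
- **The size depends on assumptions and is unadjusted.** At 90% adherence the bias is 1 to 2 points for gaps of 10 to 20 points. Carrying over pre-randomisation falling, Hoehn and Yahr score and centre would remove measured baseline selection. It would not remove unmeasured factors, or falls and illness after randomisation that lower the dose.
- **One-arm restriction is natural here**, because controls have no comparable dose. That explains the design of the contrast but does not make the groups exchangeable. Fixing the threshold a priori likewise prevents a data-driven cut-off but not selection.

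The contrast and its intended reading are both written down, so the point is not a detail merely left to an unseen analysis plan.

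**Conclusion.** The concern holds in a limited form. The planned per-protocol contrast mixes the effect of adequate dose with selection, and so cannot support the reading attached to it. With no true effect, the bias runs from about −1 point (4% false benefit) at q = 0.9 with a 10-point gap to −6 points (22%) at q = 0.7 with a 20-point gap. Against the planned 13-point effect, that is 1/13 = 8% to 6/13 = 46%. More extreme assumptions give more, and adherers at higher risk reverse the sign. The adherent share and the gap are assumptions, and the calculations are unadjusted. The documents support neither a fixed direction nor a fixed size. They do support the statement that a per-protocol effect larger than the ITT effect would not distinguish dilution from selection. The change should be made, but it concerns the interpretation of one secondary analysis; the primary ITT result stands.

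**What to change.** For the dilution question, specify a CACE (instrumental variable) analysis:

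- allocation as the instrument;
- as the treatment variable, either the adequate-dose indicator that the trial fixes a priori or the number of sessions received;
- estimation on the risk-difference scale, with the primary model's covariates;
- the exclusion restriction stated. With the adequate-dose indicator, this means that allocation has no effect on those below the threshold. With session number, linearity of the dose effect must be stated as well.

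A definition such as at least one session received is less useful: if nearly everyone starts, the estimate will lie close to ITT and say little about dilution by low dose.

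Keep the per-protocol comparison as exploratory, adjusted for the same covariates and with a caution about selection. Remove or reword the sentence that reads it as evidence on dilution.

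The cost is some wording and one extra model. The article already commits to monitoring dose and describing the extent of intervention received, so no new data collection should be needed. The downside is a wider interval and reliance on the exclusion restriction. If some benefit reaches people below the threshold, ITT/q will overstate the effect in adherers.
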